| EVALUATION CRITERIA | - PCR corrected and uncorrected clinical and parasitological cure rate at D28 and D42 ( WHO classification) - Fever and parasitological clearance (for the 1st attack) by measuring the axillary temperature and monitoring parasitemia - Proportion of afebrile patients at D3 and proportion of patients without parasites at D3 (for following attacks) - Clinical efficacy : evolution of baseline symptoms (all clinical symptoms will be graded) - Compliance based on number of residual tablets in blisters - Treatment incidence density during the 2 years of follow up (comparison of the number of malaria attacks between the two arms during the 2 years) - Mean delay between 2 attacks during the 2 years of follow up - Clinical tolerability ( incidence and intensity of recorded AE ) - Biological tolerability (Hb, Bilirubin, ALAT, Creatinine, Leukocytes, Neutrophils, and Platelets count) |
| RESCUE TREATMENT | Because PCR will not be available in real time:  Any failure before D14, will be considered as a recrudescence and will receive rescue treatment  Failure at D14 or later will be considered as reinfection; and the same ACT treatment will be repeated |
| ASSESSMENT SCHEDULE | Refer to flowchart |
| STATISTICAL CONSIDERATIONS | **Number of patients:**  With a non-inferiority margin () chosen at 5 %, =5%, and  =20%, and the hypothesis of 97% of success rate with Coartem®, 174 patients are requested; taking account of 15% of lost follow-up 200 patients are needed per treatment group.  **Statistical generalities**  All statistical analyses will be performed on SAS software (version 8.2 for PC).  All statistical tests will be bilateral and performed at a 5% significance level excepted for the non-inferiority analysis (unilateral confidence interval)  **Efficacy Analysis**  The non-inferiority of PCR adjusted adequate clinical and parasitological response at D28 (WHO protocol in vivo D28 2003) of Coarsucam® (artesunate plus amodiaquine) versus Coartem® (artemether plus lumefantrine), based on the first malaria attack of each patient will be studied using the 95% one-sided confidence interval on ITT and Per Protocol populations. |
| DURATION OF STUDY PERIOD | 2 years  Each attack will be actively followed for 42 days |

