## Inclusion criteria

### Specific inclusion criteria for initial enrollment

- Male and female children 6 to 59 months
- Confirmed mono infection with *Plasmodium falciparum*, with parasite density ≥ 2000 asexual forms per µl of blood
- Signed (or thumb-printed whenever parents/guardians are illiterate) informed consent by the parents or guardians (informed consent will be asked only at recruitment and will cover the whole period of the study, including subsequent follow up).
- Parents’ or guardians’ willingness and ability to comply with the study protocol for the duration of the trial.

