### Secondary criteria

For the first episode:

- Clinical and parasitological efficacy is defined by grading clinical signs further to an interview by the investigator, together with the values obtained for temperature and parasitaemia before and after PCR correction at D42, and before PCR correction at D28
- Monitoring of parasitaemia during the different visits in order to define clearance
- Measure of axillary temperature at each visit in order to define the clearance of fever
- Monitoring of gametocytaemia during each evaluation

For the following episodes:

- Clinical and parasitological effectiveness is defined by grading the clinical signs further to an interview by the investigator, together with the values obtained for temperature and parasitaemia before and after PCR correction at D28 and D42
- Proportion of patients without fever at D3 obtained with the values of temperature (axillary temperature<37.5°C)
- Proportion of patients without parasites at D3 (negative thick smear)

During the total follow up of the cohort:

- Compare the number of malaria attack for each patient between two arms and mean delay between 2 attacks during the 2-years of follow up
- Compare the number of patients with anemia at D0 of each episode during the 2 years per arm.
- Compare the evolution of anaemia by patient between D0 and D28 for each episode

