## Statistical methods

All statistical analyses will be performed on SAS software (version 8.2 for PC).

All statistical tests will be performed at a 5% significance level and will be bilateral except for the non-inferiority analysis (unilateral confidence interval).

Distributions of parameters will be summarized by mean, standard deviation, median, minimum and maximum. These distributions will be compared using the Student t-test if normal distribution hypothesis is confirmed. Otherwise, distributions will be compared using the non-parametric Wilcoxon test.

All qualitative parameters will be summarized in contingency tables displaying frequencies and corresponding percentages.

For these parameters, a chi-square test (replaced by Fisher exact test if the expected frequency in any one of the cells of the contingency table is < 5) will be performed.

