#### Analysis of secondary efficacy variables

Non inferiority analysis will be performed on the same way than for the main criterion for

- before PCR corrected cure rate at D28 for the first attack
- before and after PCR corrected cure rate at D28 for the following attacks
- before and after PCR corrected cure rate at D42 for all attacks

An analysis for repeated measurements will be performed. A model will be built in order to explain the success/failure of the response. The rank of the attack, the group of treatment and their interaction will be included in the model. Some other relevant parameters could be included if descriptive analysis find out discriminating items.

Comparison between treatment groups will be provided for the following parameters

- Time to parasitological clearance for the 1st episode (number of patients without parasite from D1 to D3)
- Time to fever clearance for the 1st episode (number of patients without temperature from D1 to D3)
- Proportion of patients without fever at D3 for repeated attacks
- Proportion of patients without parasite at D3 for repeated attacks
- Evolution of number of gametocyte carriers and mean values of gametocyte rate during the 42 days of follow-up for each episode
- Evolution of hemoglobin value for each patient during each attack (between D0 and D28) occurring during the 2 years of follow up
- Evolution of mean hemoglobin values at D0,D3, D7,D14 and D28 of each episode during the 2 years of follow up
- Evolution of Hackett score during the 2 years of follow up

The number of malaria attacks will be summarized by treatment group and overall.

The evolution of average duration between 2 attacks during the 2 years of follow up will be computed and analyzed using survival analysis methods.

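### The 2-year attack count is meant to be compared between arms, but the only test rule that covers it is unadjusted: it gives no rate ratio and leaves age at enrolment unused, at some cost in precision

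*Protocol*

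**What the plan says.** The Synopsis lists treatment incidence density among the evaluation criteria and explains it as "comparison of the number of malaria attacks between the two arms during the 2 years". Section 10.1.2 sets the same aim among its cohort-level criteria: "Compare the number of malaria attack for each patient between two arms and mean delay between 2 attacks during the 2-years of follow up". Section 6.2 names it as a cohort objective.

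Section 14.5.3.2 has a list of parameters for which a comparison between groups is promised. The attack count is not in that list. It follows in a separate sentence: "The number of malaria attacks will be summarized by treatment group and overall". The interval between attacks gets survival methods; the count gets no test or model.

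The general rule in section 14.5 covers quantitative variables. Where normality is accepted it says: "These distributions will be compared using the Student t-test if normal distribution hypothesis is confirmed". For all other cases the fallback is a rank test: "Otherwise, distributions will be compared using the non-parametric Wilcoxon test". Neither test takes a covariate. Section 14.5.3.2 does allow covariates in the success/failure model, but only optionally and after looking at the data: "Some other relevant parameters could be included if descriptive analysis find out discriminating items". That sentence does not reach the attack count.

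On age, section 8.2.1 enrols "Male and female children 6 to 59 months", section 13.2.1 records age at D0, and section 9.2 describes a randomisation list for two groups without mentioning stratification. Section 14.5.1 checks baseline comparability but does not link that check to an adjusted analysis.

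**The concern.** Sections 10.1.2 and 14.5.3.2 do not match: one intends a comparison, the other offers a summary. Closing the gap with the general rule gives a t-test or rank test on what are likely to be skewed counts. The objective is an incidence density, for which the natural estimate is a rate ratio with an interval, and the rule does not supply one.

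The rule also leaves unused a baseline variable that every child has. Oldest to youngest at enrolment is 59/6, almost tenfold. If attack frequency varies with age, that variation stays in the error term and the comparison is less precise than the same data allow. At stake is the sharpness of a secondary cohort result, not the D28 non-inferiority conclusion.

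**Working it through.** **The plan's own figure.** The protocol states no sample size, rate or effect for the attack count. Its only sizing figure is 174 per arm, raised to 200, for the primary endpoint (section 14.2). A Farrington-Manning calculation with 97.3% success, a 5-point margin, one-sided 5% and 80% power gives 171, within 3% of 174 (183 at 97%; simpler unpooled formulas give 130 and 144). This does not bear on the attack count.

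**Inputs from the protocol.** 200 per arm; two-sided 5% for secondary tests; age 6 to 59 months.

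**Inputs that must be assumed.** Mean attacks per child, overdispersion, and the change in attack rate with age. Age is taken as uniform on 6 to 59 months.

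**Is the unadjusted test valid?** In 2,000 simulated null trials per setting (mean 5, overdispersion 0.5, attack-rate ratio 0.8 or 0.6 per year of age), type I error was 4.4-4.6% for the t-test and 4.5-5.2% for Wilcoxon. The level holds even with a strong age effect.

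**How large can a chance age imbalance be?** The SD of age is 53/√12 = 15.3 months. The SE of the difference in mean age is 15.3 × √(2/200) = 1.53 months, so the 95% range is ±1.96 × 1.53 = ±3.0 months. At that limit the attack-rate ratio moves by a factor r^(3.0/12), where r is the rate ratio per year of age: 2.6% for r = 0.9, 5.4% for 0.8, 8.5% for 0.7, 12% for 0.6. The unadjusted standard error already includes this variation.

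**How much precision does adjustment recover?** Let a child's expected count be λ, with mean m over the age range and variance V due to age, and let residual overdispersion be k.
- Unadjusted variance per child on the log scale: vu = [V + m + k(m² + V)] / m².
- Age-adjusted negative binomial: va = 1 / E[λ/(1 + kλ)].
- SE of the log rate ratio with 200 per arm: √(2v/200).

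Example with m = 5, k = 0.5, r = 0.8 per year (0.8^(53/12) = 0.373, so 2.7-fold from youngest to oldest): V = 1.99, and the residual part is 5 + 0.5 × (25 + 1.99) = 18.50.
- vu = (1.99 + 18.50)/25 = 0.820, SE = 0.0905.
- va = 0.712, SE = 0.0844.
- Variance saved: 1 − 0.712/0.820 = 13%.

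Over means of 2 to 9 and k of 0.2 to 1.0, the same formulas give:

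| Rate ratio per year of age | Fold change, 6 to 59 months | Variance saved |
|---|---|---|
| 1.0 | 1.0 | none |
| 0.9 | 1.6 | 2-6% |
| 0.8 | 2.7 | 8-22% |
| 0.7 | 4.8 | 17-41% |
| 0.6 | 9.5 | 28-56% |

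Simulated trials over a narrower range (200 per arm, true rate ratio 0.85, mean 4 or 8, frailty variance 0.2 to 0.4) gave model-based savings of 2-4% for a 1.5-fold gradient, 5-10% for 2-fold and 12-21% for 3-fold. That is the source of the 2-21% range.

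**The case against.** The strongest reply is that covariates for a secondary endpoint are commonly left to the statistical analysis plan, which is not shown. Nothing in the protocol forbids adjustment, and Wilcoxon is a sound test for skewed counts. This largely stands: the absence of a named covariate is not an error in itself. What remains is that the protocol is not silent. It promises a comparison in one place and a summary in another, supplies a covariate-free rule between them, and in section 14.1 makes Section 14 the basis of the later plan.

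A reader might infer that the quoted sentence itself prescribes an unadjusted comparison. It does not; it describes a summary, and the unadjusted test follows only from reading section 10.1.2 with section 14.5.

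A reader might also infer that a chance age difference would pass for a drug effect, so that the comparison is biased. The documents do not support that. Under randomisation such imbalance is sampling variation that the test allows for, as the type I error above shows.

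Finally, a large power gain is tempting to quote. At a mean of 8, frailty variance 0.2 and a 3-fold gradient, one set of 300 simulated trials gave power of 77% adjusted, 62% unadjusted negative binomial and 58% Wilcoxon; a second set of 400 gave 80%, 69% and 65%. That is the most favourable setting examined, each figure carries 2 to 3 points of simulation error, and the true ratio of 0.85 is itself assumed. It illustrates and does not estimate.

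**Conclusion.** The point holds as a low-cost improvement to a secondary analysis. As written, the comparison of attack counts falls to an unadjusted test that yields no rate ratio and ignores age at enrolment. The test is valid; the cost is precision.

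The size rests wholly on assumptions. It is nil if attack rate does not vary with age over 6 to 59 months, and about 2-21% of the variance of the log rate ratio for 1.5- to 3-fold gradients at the means and frailty variances simulated. It would be larger only with steeper gradients or less residual variation relative to the mean. The protocol gives no age gradient to choose among these. The primary D28 conclusion is unaffected.

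**What to change.** In section 14.5.3.2, state that the number of attacks is compared between arms by negative binomial regression, with treatment and age at enrolment as prespecified terms and log follow-up time as offset, reporting the rate ratio with its 95% confidence interval. Keep the summary by group as description.

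The offset is needed. Without it the model gives a ratio of mean counts, not a ratio of rates, and follow-up differs between children. Section 8.1 counts the 2 years from the first patient's enrolment and allows four months of recruitment, so a child who stays in has about 20 to 24 months. Section 7.2 speaks of 2 years per child, but the withdrawals in section 12.2 make follow-up unequal in any case.

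Naming age in advance also avoids choosing covariates after seeing the data. The cost is wording, slightly more analysis work and reliance on a model; no further patients, visits or measurements are required.

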### Analysis of safety data

This analysis will be performed on the safety population.

#### Analysis of adverse events

Treatment-emergent AEs (TEAEs) are defined as AEs that developed or worsened during the study period (time from first dose of study medication up to D42 days after the first dose of study medication) for each attack.

All adverse events will be coded using MedDRA. The following frequency distributions of adverse events (incidence tables) will be provided for the safety population:

- All and possibly related TEAEs by system organ class,
- Possibly related TEAEs by system organ class and by decreasing frequency,
- All and possibly related TEAEs by intensity and system organ class,
- Serious adverse events: All and possibly related TEAEs by seriousness criterion,
- Serious adverse events: All and possibly related TEAEs by system organ class,
- Death: All and possibly related TEAEs by system organ class,
- Other significant adverse events: All and possibly related TEAEs by “other significant” adverse event criterion,
- Discontinuation: All and possibly related TEAEs by system organ class,
- Laboratory abnormalities: All and possibly related TEAEs,

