## Duration of study

Thescheduled duration of the study is 2 years. Each malaria attack that occurs during this period will be followed for 42 days.

Each new malaria attack occurring at least 14 days after the previous one will be considered as a reinfection, will be therefore treated with the same drug and followed up during 42 days.

All patients presenting to the study clinic with a new episode of fever will undergo standard evaluation (history, physical examination and Giemsa-stained blood smear) for the diagnosis of malaria. Participants will be randomized to one of two combination treatment regimens at the time of their first diagnosis of uncomplicated malaria. Each patient will be followed up actively after recruitment for 42 days (first follow up) and then passively for 2 years. If within the 2-year period the patient presents with a new malaria attack, he/she will be enrolled again in the study. At each episode the patient will receive the same drug.

Participants will be followed for 2 years for all routine medical care in the study clinic. All subsequent episodes of uncomplicated malaria will be treated with each participant’s assigned treatment regimen. All clinical treatment failures occurring within 14 days of diagnosis and all episodes of complicated malaria will be treated with quinine, the standard therapy for malaria after treatment failure in Uganda. All episodes diagnosed more than 14 days after a previous episode will be considered new episodes for treatment purposes.

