### Management of treatment failures

Patients treated for uncomplicated malaria that are classified as failures (within 14 days of treatment) will be treated with quinine (10 mg/kg TID x 7d). In the unlikely event that a patient fails to have an adequate clinical response to quinine (either as first-line therapy for complicated disease or second-line therapy), treatment will be repeated with quinine (3 days) and clindamycin (5 mg/kg QID for 7 days). In this case, a failure CRF will be completed and patient will be followed-up until D42 from the initial enrolment Safety medication will be recorded in the failure case report form.

In experience of the site, failure to respond to quinine therapy is generally an indication of non-compliance. In the very unlikely event that a patient fails to have an adequate clinical response to quinine plus clindamycin therapy or if they develop severe or complicated malaria, they will be referred to Nagongera Health Centre IV or Tororo Hospital for further evaluation.

Treatment failures occurring on D14 or later have to be considering as reinfections and have to be treated with the same ACT allocated by the randomisation.

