### Impact of repeated treatment on clinical and biological tolerability

All adverse events will be catalogued based on their frequency, severity, and relationship to study medication using standardized protocols (Appendix 2). These indices of safety and tolerability among treatment groups will be compared using each episode of malaria treated with a study drug as the unit of analysis. The same analyse will be done with the biological parameters.

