# Patient safety

## Safety instructions

Safety and tolerability of the treatments will be evaluated by recording Adverse Events (AEs) and grading laboratory and vital signs evaluations. A severity grading scale, based on toxicity grading scales developed by the WHO and the National Institutes of Health, Division of Microbiology and Infectious Diseases, will be used to grade severity of all symptoms, physical exam findings, and haemoglobin results (see Appendix 2 and 3).

All laboratories abnormalities on D28 (ref: Appendix 3)

- Grade 2 or more for biological data
- Clinically significant abnormality (whatever the grade)

have to be followed until resolution or progression has to be stabilized.

For each malaria episode, follow-up for safety will be conducted during the scheduled malaria follow-up visits, and at any unscheduled visit. Follow-up for adverse events reported during a given malaria episode will continue until the patient is re-treated with study medications, or the study ends. If an AE is on going at the time of inclusion for a new malaria episode this AE will be recorded as a concomitant disease at D0 (the AE number recorded at the episode where this AE occurred will be specified to link them). At each episode a new cycle of adverse event assessment and reporting will begin according to the definitions of AE and SAE. Each AE will be considered as one until it has recovered.

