## Obligation of the Investigator regarding safety reporting

***Adverse Events***

All Adverse Events regardless of seriousness or relationship to Investigational Product, spanning from the first visit planned in the Clinical Trial Protocol/signature of the informed consent form, up to the last visit planned in the protocol (D42), are to be recorded on the corresponding page(s) included in the Case Report Form.

Whenever possible, symptoms should be grouped as a single syndrome or diagnosis. The Investigator should specify the date of onset, intensity, action taken with respect to Investigational Product, corrective treatment/therapy given, additional investigations performed, outcome and his/her opinion as to whether there is a reasonable possibility that the Adverse Event was caused by the Investigational Product.

Laboratory, vital signs abnormalities are to be recorded as Adverse Events only if they are medically relevant: symptomatic, requiring corrective treatment, leading to discontinuation and/or fulfilling a seriousness criterion and/or is defined as an AESI.

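### Each attack's adverse-event window runs to D42 although a new course can start from about D14: windows overlap as defined or, read with section 11.1, are unequal in length, and neither suits a per-episode comparison of tolerability

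*Protocol*

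**What the plan says.** Section 14.5.4.1 defines treatment-emergent events separately for each attack, as those developing or worsening during the "time from first dose of study medication up to D42 days after the first dose of study medication". Section 11.7 has the investigator record all events "up to the last visit planned in the protocol (D42"). Section 7.2 matches this: "Each malaria attack that occurs during this period will be followed for 42 days".

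A second course can begin inside those 42 days. The Synopsis says "Failure at D14 or later will be considered as reinfection; and the same ACT treatment will be repeated", section 7.2 says "Each new malaria attack occurring at least 14 days after the previous one will be considered as a reinfection", and section 9.7.4 says "Treatment failures occurring on D14 or later have to be considering as reinfections and have to be treated with the same ACT allocated". Each such recurrence is a new attack with its own follow-up.

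Section 11.1 sets a different end point: "Follow-up for adverse events reported during a given malaria episode will continue until the patient is re-treated with study medications, or the study ends". It adds that a new cycle of assessment and reporting opens at each episode, that an event still ongoing is carried to the new D0 as a concomitant disease linked by its number, and that an event counts as one until recovery.

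Section 10.2.3 compares the groups on these indices "using each episode of malaria treated with a study drug as the unit of analysis". It does not mention days at risk.

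**The concern.** The definition in 14.5.4.1 and the re-treatment rule together give one child overlapping windows, and nothing says which attack owns an event that starts after the second course but within D42 of the first. The linking rule in 11.1 covers events already ongoing at re-treatment, which is a different case. If the new-cycle rule is taken to close the earlier window, double assignment disappears, but a re-treated attack then has fewer days in which an event can occur.

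Tolerability in repeated attacks and the impact of repeated treatment are stated objectives (section 6.2). Treatment incidence density is also compared between arms, and section 14.5.3.2 analyses the interval between attacks. So an outcome that may differ by drug also determines the length or overlap of the safety windows. Section 5.5 describes holoendemic transmission, with an annual inoculation rate above 400 for one vector, so early recurrence is plausible, though the protocol gives no figure for it.

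**Working it through.** The plan gives no figure on this point to reproduce.

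**Inputs.** From the protocol: window 42 days; earliest repeat course about D14. Assumed, because the protocol gives no values: probability p of re-treatment between D14 and D42, from 10% to 60%, with constant hazard h after D14; background event rate b of 0.01 to 0.02 per day; e = 0 to 0.5 extra events per course, spread over the first 7 days after dosing. Drug safety is identical in both arms throughout.

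**1. Overlap.** Re-treatment on day d leaves 42 - d shared days.
- D14: 28 days, 28/42 = 67%
- D21: 21 days, 21/42 = 50%
- D28: 14 days, 14/42 = 33%

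With courses at D0, D14 and D28, an event starting between D28 and D42 lies in three windows.

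**2. Days at risk if windows are cut at re-treatment.** h = -ln(1 - p)/28, and mean days = 14 + p/h.
- p = 20%: h = 0.00797, mean = 14 + 0.2/0.00797 = 39.1
- p = 50%: h = 0.02476, mean = 14 + 0.5/0.02476 = 34.2

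**3. Events per attack, cut windows:** b x mean days + e. With b = 0.02 and e = 0.3:
- p = 20%: 0.02 x 39.1 + 0.3 = 1.08
- p = 50%: 0.02 x 34.2 + 0.3 = 0.98

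The arm re-treated sooner shows about 9% fewer events per attack.

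**4. Events per attack, full windows:** 42b + e(1 + m). Here m is the expected number of later courses whose early events fall inside the window: P(second course started by day 42 - u) + P(third course started by day 42 - u), averaged over u from 0 to 7. This gives m = 0.181 at p = 20% and 0.483 at p = 50%.
- p = 20%: 0.84 + 0.3 x 1.181 = 1.19
- p = 50%: 0.84 + 0.3 x 1.483 = 1.28

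That is about +8%. A simulation over 2 years with 1,500 children per setting gave 1.18 v 1.27, or +7%, which agrees within simulation error.

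**5. Sensitivity, 20% v 50% re-treated, by the same formulas.**

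| b, e | Full windows | Cut windows |
| --- | --- | --- |
| 0.02, 0 | 0.84 v 0.84 (none) | 0.78 v 0.68 (about -13%) |
| 0.02, 0.3 | 1.19 v 1.28 (+7% to +8%) | 1.08 v 0.98 (-9%) |
| 0.01, 0.5 | 1.01 v 1.16 (+15%) | 0.89 v 0.84 (-5%) |

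With e = 0, full windows give 42b in both arms whatever the overlap. The two readings shift the comparison in opposite directions whenever e > 0.

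**6. Events lying in more than one window** (simulation, b = 0.02, e = 0.3): 5%, 9%, 15%, 22%, 28% and 35% for p = 10%, 20%, 30%, 40%, 50% and 60%.

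**7. Common early window,** first dose to before D14: 14b + e = 0.28 + 0.3 = 0.58 in both arms, whatever p is.

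**The case against.** The best reply is that section 11.1 already settles most of this. A new cycle opens at each episode, ongoing events are linked, and each event counts once. The sentence on follow-up concerns events already reported, whereas 14.5.4.1 decides which onsets are treatment-emergent. Read together, the two could mean the earlier of re-treatment and D42. Detailed window conventions usually belong in the SAP, which is not at hand, and onset dates are collected, so nothing would be lost.

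Much of that stands. A reader might infer that the protocol plans to count events twice. It does not say so; double assignment follows only from applying 14.5.4.1 literally by onset date. A reader might also infer that reinfection timing turns into a safety difference whichever rule is used. Step 5 shows otherwise: with full windows and a constant event rate there is no distortion between arms. An arm always re-treated at day 21 set against one always re-treated at day 42 would show 21r v 42r events per attack under cutting, for an event rate r per day. That two-fold gap is a constructed extreme; the documents give no re-treatment interval and no difference between arms.

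What does not stand is that only a detail is missing. The protocol fixes a window that overlaps as written, the reading through 11.1 leaves windows of unequal length, and the per-episode comparison in 10.2.3 adjusts for neither. Section 14.1 makes section 14 the basis of the SAP, so the mismatch is carried forward.

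**Conclusion.** The point holds in a limited form. As written, windows can overlap by up to 28 of 42 days, and one event can be treatment-emergent for two or more attacks. Under the 11.1 reading, per-episode counts favour the arm re-treated sooner. Under full windows, a distortion between arms needs events that cluster after dosing.

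For an assumed 20% v 50% re-treated between D14 and D42, with background 0.02 per day and 0.3 early events per course, the shifts are about +7% (full) and -9% (cut). Other assumed event rates give 0 to +15% and -5% to -13%. If the arms are re-treated at the same pace, neither rule biases the comparison between them, although double assignment remains. The documents do not show that the pace will differ; they only plan to compare it.

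The primary first-attack efficacy analysis is untouched. This should be corrected because the comparison affected is a stated objective and the repair is cheap.

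**What to change.** Reconcile sections 11.1, 11.7 and 14.5.4.1 so that, for analysis, each attack's window ends at the earlier of D42 and the first dose of the next course, and each event is assigned by onset date to the most recent course. In 10.2.3 and 14.5.4.1, compare arms per attack over a common early window that every attack has, for example first dose to before D14. Report events per child-day over the full truncated window alongside, by arm and attack rank.

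The cost is wording and simple programming. Section 11.6 already collects onset dates, and treatment dates are recorded. There are two drawbacks. Late effects of an earlier course are assigned to the later one; a listing can show these. The child-day rate also still depends partly on re-treatment timing if events cluster after dosing: with the step 3 inputs it is 1.082/39.1 = 0.0277 v 0.984/34.2 = 0.0288, about 4% higher in the arm re-treated sooner. In the 21 v 42 day extreme it is 0.72/21 = 0.034 v 1.14/42 = 0.027. That is why the common early window should carry the comparison and the rate should support it. No change to when children are re-treated is implied.
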